# Perioperative use of crystalloids in patients undergoing open radical cystectomy: balanced Ringer’s maleate versus a glucose 5%/potassium-based balanced solution: study protocol for a randomized controlled trial

**DOI:** 10.1186/1745-6215-15-276

**Published:** 2014-07-08

**Keywords:** Crystalloid solution, Return of the gastrointestinal function, Radical cystectomy

## Abstract

**Background:**

The optimal crystalloid solution to use perioperatively in patients undergoing open radical cystectomy remains unclear. Many of the fluids used for intravenous hydration contain supraphysiologic concentrations of chloride, which can induce hyperchloremia and metabolic acidosis, resulting in renal vasoconstriction and decreased renal function. In addition, patients receiving less fluid and less sodium show faster recovery of gastrointestinal (GI) function after colonic surgery.

**Methods and design:**

This is an investigator-initiated, single-center, randomized, controlled, parallel group trial with assessor-blinded outcome assessment, in the Department of Urology, University Hospital Bern, Switzerland. The study will involve 44 patients with bladder cancer scheduled for radical cystectomy and urinary diversion. The primary outcome is the duration between the end of surgery and the return of the GI function (first defecation). Secondary outcomes are fluid balance (body weight difference postoperatively versus preoperatively) and the incidence of kidney function disorders according to the Risk – Injury – Failure – Loss - End Stage Renal Disease (RIFLE classification). An equal number of patients are allocated to receive Ringerfundin® solution or a glucose/potassium-based balanced crystalloid solution as baseline infusion during the entire time that intravenous administration of fluid is necessary during the perioperative period. The randomized crystalloid solution is infused at a rate of 1 ml/kg/h until the bladder has been removed, followed by 3 ml/kg/h until the end of surgery. Postoperative hydration is identical in both groups and consists of 1,500 ml of the randomized crystalloid solution per 24 hours. Postoperative patient care is identical in both groups; patients are allowed to drink clear fluids immediately after surgery, and liquid diet is started on postoperative day 1, as well as active mobilization and the use of chewing gum. Body weight is measured daily in the morning. Time of first flatus and first defecation are recorded.

**Discussion:**

This trial assesses the benefits and harms of two different balanced crystalloid solutions for perioperative fluid management in patients undergoing open radical cystectomy with urinary diversion, with regard to return of GI function and effects on postoperative renal function.

**Trial registration:**

Current Controlled Trials ISRCTN32976792 (registered on November 21 2013).

## Background

A recent randomized double-blind clinical trial has demonstrated that intraoperative restrictive hydration with a maleate Ringer’s solution (Ringerfundin®) combined with a concomitant norepinephrine infusion reduces the incidence of postoperative complications and hospitalization time [1]. Patients to whom restrictive hydration was administered were more inclined to have a postoperative zero fluid balance (i.e. weight difference on postoperative day (POD) 1 versus preoperatively was 0) compared with patients in the control group, who had a positive fluid balance of approximately 2 kg on POD 1. A positive postoperative fluid balance is known to be associated with increased postoperative complications [2]. In addition, the intraoperative use of norepinephrine, by minimizing the risk of fluid overload, is associated with a lower incidence of acute kidney damage [3].

Although enough evidence exists to support the rational use of perioperative restrictive hydration, the choice of the optimal crystalloid solution to use remains unclear, and intravenous chloride administration is ubiquitous [4]. Many of the fluids used for intravenous hydration contain supraphysiological concentrations of chloride, which can induce hyperchloremia and metabolic acidosis, resulting in renal vasoconstriction and decreased renal function [5]. The effect of chloride on the kidney is of concern because acute kidney injury has been associated with high mortality, and may require invasive renal replacement therapy [6,7]. After administration of NaCl 0.9%, glucose 5% and Ringer’s lactate solutions in normal subjects, the physiological response is a slow excretion of sodium, which can be impaired by hyperchloremia [8,9]. Because patients undergoing cystectomy are prone to have transient creatinine increase, electrolyte disturbance, and acidosis postoperatively, it would make sense to administer a more physiological intravenous solution to these patients perioperatively. In addition, it has been demonstrated that the influence of salt and water balance on gastrointestinal (GI) recovery after colonic surgery is clinically relevant: patients receiving less fluid and less sodium show faster recovery of GI function, resulting in a shorter hospitalization time [10]. This is of crucial importance in patients undergoing cystectomy because they are at risk for postoperative constipation or ileus.

The aim of this study is to evaluate, in a prospective, single-center, randomized, parallel-group, assessor-blinded study design, the physiology of electrolyte and water homeostasis in patients undergoing open radical cystectomy and urinary diversion, using two different fluid regimens. We hypothesize that an approach with a glucose/potassium-based and reduced chloride crystalloid solution will result in faster return of GI function, reduced hypernatremia and hyperchloremic metabolic acidosis, less frequent hyperosmolality, and a better maintained fluid balance compared with a regimen using a balanced Ringer’s crystalloid solution.

## Method and design

### Ethics approval

The study was approved by the local ethics committee (Kantonale Ethikkommission Bern KEKBE; chairperson: [name] [name]; registration number 151/13) on October 22, 2013. This study is conducted in accordance with the Declaration of Helsinki and was prospectively registered on November 21, 2013 at http://www.controlled-trials.com/isrctn with the trial identification number ISRCTN32976792.

### Objectives of the study

The main objectives of this study are 1) to analyze if a positive salt and water balance is associated with a delayed return of GI function; 2) to compare arterial pH, electrolyte (Na, K, Cl, Mg, HPO_4_), glucose, and bicarbonate concentrations at 6 h, 24, 48, 72 and 96 hours postoperatively; 3) to measure sodium and water excretion over the same time period; 4) to study the effect of these crystalloid solutions on plasma osmolality, levels of brain natriuretic peptide (BNP), and plasma concentration of the hormones controlling water and sodium excretion (plasma renin, aldosterone, arginin-vasopressin); and 5) to measure the urine osmolality and concentration of Na, Cl and neutrophil gelatinase-associated lipocalin (NGAL).

### Study endpoints

The primary outcome variable is the postoperative return of GI function after open radical cystectomy, defined as the first defecation and expressed in days.

Secondary outcome variables are postoperative first flatus, positive fluid balance (body weight difference postoperatively versus preoperatively); incidence of kidney function disorders according to the RIFLE classification [11]; difference in pH 24 hours postoperatively (metabolic acidosis defined as hyperchloremia, normal anion gap, low plasma bicarbonate); changes in plasma and urine osmolality during the duration of infusion; incidence of hypernatremia during the duration of infusion; incidence of hyperchloremia during the duration of infusion; incidence of hypokalemia or hyperkalemia during the duration of infusion; changes in plasma renin, aldosterone, arginin-vasopressin, and BNP levels; and changes in NGAL urine values.

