### Statistics

Data will be analyzed by the research team in collaboration with a medically versed biostatistician. There will be no interim analysis.

Statistical analysis will be conducted on an intention-to-treat basis. Data distribution will be tested by Q-Q plots. Normally distributed data will be presented as mean and standard deviation (SD), skewed data as median and range, and dichotome data as number and percentage. Comparing related and unrelated continuous samples, the paired and unpaired *t*-tests, respectively, will be used for normally distributed data and the Wilcoxon signed rank test and Mann–Whitney *U*-test, respectively for skewed data. Differences in proportions will be analyzed using the Fisher’s exact test, and risk ratio with associated 95% confidence interval (CI). For the analysis of the primary endpoint, we will use the unpaired Student *t*-test with associated 95% CI. In addition, a multiple logistic regression analysis will be carried out, including the randomization groups and all clinically relevant variables (age, ASA scores, Charlson comorbidity score, Glasgow prognostic score, postoperative fluid balance). A two-sided *P* value of less than 0.05 will be considered significant.

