### Sample analysis

Based on retrospective data from our institution in the same surgical population (mean duration until first defecation 4.82 days, SD of 0.82 days), a power analysis was performed using duration of return of GI function as the primary variable. For a calculated sample size of 18 patients in each group (36 patients in total) the study is designed to have an 90% power (β = 0.10) for the Wilcoxon/Mann–Whitney test to detect a difference of 1 day between the groups (Ringerfundin® and G5-K solution) at a two-sided significance level of 5% (α = 0.05) assuming an SD of 1 day (G Power Version 3.1.5., Kiel and Duesseldorf, Germany). This decrease of 1 day is considered clinically relevant. Assuming a drop out of 20%, 22 patients per group will be recruited.

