## Conclusion

In conclusion, this trial is an investigator-initiated, pragmatic, randomized clinical trial to test the hypothesis that administration of glucose-rich balanced crystalloid solution containing potassium can accelerate the return of GI function. In addition, this study will also determine the effect of this solution on renal function after radical cystectomy with urinary diversion.

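### Kidney function is assessed only as a RIFLE incidence in 18 to 22 patients per group, which cannot support the statement that the trial will determine the effect on renal function

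*Protocol article*

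**What the plan says.** Study endpoints lists, among the secondary outcomes, "incidence of kidney function disorders according to the RIFLE classification [11". The Abstract names it as one of only two secondary outcomes. The Statistics section does not mention RIFLE by name, but an incidence is a proportion and so falls under this rule: "Differences in proportions will be analyzed using the Fisher’s exact test, and risk ratio with associated 95% confidence interval (CI". The threshold is general: "A two-sided *P* value of less than 0.05 will be considered significant".

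Two other kidney-related entries are continuous. Study endpoints includes "changes in NGAL urine values", and Objectives of the study includes the aim "to measure the urine osmolality and concentration of Na, Cl and neutrophil gelatinase-associated lipocalin (NGAL". The objectives also include sodium and water excretion.

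The trial is sized on time to first defecation alone: "For a calculated sample size of 18 patients in each group (36 patients in total"), raised to 22 per group for dropout. No RIFLE rate, target difference or power is stated. The Background expects a graded change, since "patients undergoing cystectomy are prone to have transient creatinine increase, electrolyte disturbance, and acidosis postoperatively". The Conclusion then states that "this study will also determine the effect of this solution on renal function after radical cystectomy with urinary diversion".

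**The concern.** RIFLE grades a change in kidney function. Counting patients with any disorder reduces that change to yes or no, and in a trial of 44 patients the count will be small. Other physiological outcomes in the article (osmolality, renin, aldosterone, BNP, NGAL) are followed as changes on their own scale, but no such comparison is listed for kidney function.

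The Abstract, Discussion and Conclusion all present renal function as a second question that the trial will address. If the fluids differ materially, the most likely result is still a non-significant Fisher test with a very wide risk ratio. After a promise to determine the effect, a reader could take that result as evidence that the fluids do not differ for the kidney.

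**Working it through.** **Inputs from the article.** Evaluable patients: 18 per group. Recruited: 22 per group (18 × 1.2 = 21.6, rounded up). Two-sided 5% level. Fisher's exact test for proportions. The plan states no renal power, so there is no figure of its own to reproduce; its 90% refers to first defecation.

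**Assumed.** All RIFLE rates below.

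**Step 1: power of Fisher's test.** Add Bin(i; n, p1) × Bin(j; n, p2) over all tables (i, j) whose two-sided Fisher P value is at or below 0.05.

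**Step 2: continuous comparator, model A.** Suppose RIFLE is a cut of a normal measure with equal SD, and the fluid shifts every patient equally. The standardised shift is d = z(1 − p2) − z(1 − p1). For 20% against 5%, d = 1.645 − 0.842 = 0.80. The t-test has noncentrality d√(n/2), here 0.80 × √11 = 2.66 on 42 degrees of freedom at 22 per group, and its power is 74%.

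| Assumed rates | d | Fisher, n=18 | t-test, n=18 | Fisher, n=22 | t-test, n=22 |
|---|---|---|---|---|---|
| 20% vs 5% | 0.80 | 13% | 65% | 20% | 74% |
| 30% vs 10% | 0.76 | 21% | 60% | 28% | 69% |
| 40% vs 15% | 0.78 | 27% | 63% | 35% | 72% |
| 50% vs 20% | 0.84 | 36% | 69% | 43% | 78% |
| 30% vs 5% | 1.12 | 38% | 90% | 51% | 95% |
| 20% vs 10% | 0.44 | 6% | 25% | 9% | 30% |
| 30% vs 20% | 0.32 | 5% | 15% | 7% | 18% |

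For the first five rows the gain is 33 to 54 points over both group sizes. For the last two it is about 10 to 21 points, and power stays at 30% or less on either scale. Fisher's test does better only for very large contrasts: at 22 per group, 79% for 50% vs 10% and 77% for 40% vs 5%.

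**Step 3: a different mechanism, model B.** Suppose most patients vary around no change, a minority have a clear rise, and the fluid changes only how many are in that minority. Simulation used 22 per group, the five large pairs, rises of 0.6 or 0.8 in log ratio and SD 0.12 or 0.20. Two of the four settings are shown:

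| Assumed rates | Fisher | t-test (rise 0.6, SD 0.12) | t-test (rise 0.8, SD 0.20) | Mann–Whitney, about |
|---|---|---|---|---|
| 20% vs 5% | 20% | 23% | 21% | 13% |
| 30% vs 10% | 28% | 32% | 29% | 20% |
| 40% vs 15% | 35% | 40% | 37% | 29% |
| 50% vs 20% | 43% | 49% | 46% | 40% |
| 30% vs 5% | 51% | 51% | 45% | 29% |

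Here the t-test differs from Fisher by about −5 to +6 points. The clearest setting (rise 0.8, SD 0.12) gives up to +9. The noisiest (rise 0.6, SD 0.20) falls below Fisher throughout, by 13 points for 30% vs 5%. The Fisher column assumes error-free classification, which favours Fisher in that last setting. Mann–Whitney, which the Statistics section assigns to skewed data, is below Fisher in every row.

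**Step 4: what the report would show.** Take 6/22 against 2/22 as an illustration. The risk ratio is 3.0. The SE of its log is √(1/6 − 1/22 + 1/2 − 1/22) = 0.76. The 95% CI is exp(1.099 ± 1.96 × 0.76), about 0.7 to 13. A threefold excess would be non-significant and compatible with anything from a modest reduction to a very large increase.

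**The case against.** The strongest reply has four parts.

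- **The endpoint is legitimate.** RIFLE is a cited classification and a clinical event, it is secondary, and no power is claimed for it. Low power for a secondary outcome is not an error, and the planned risk ratio with 95% CI will show the imprecision. This stands. It is why the RIFLE comparison should stay, and why the fault lies in the Conclusion's wording and the missing continuous companion, not in a wrong calculation.
- **The gain depends on the model.** The large figures come from an equal shift in every patient, which nothing in the article supports, and they shrink or vanish under model B. This also stands. A reader might infer from step 2 that the binary analysis costs a fixed 33 to 54 points; the documents give neither the rates nor the mechanism to say so.
- **Kidney measures are already continuous.** NGAL, sodium and water excretion and urine osmolality are kept on their full scale. A reader might therefore go too far and say that the kidney is assessed only by RIFLE. That is not so. These entries nevertheless describe injury or excretion and do not replace a comparison of the function measure that RIFLE grades.
- **Creatinine is not in the listed samples.** Correct, but RIFLE grading needs a kidney-function measure, and an article may condense its sampling lists. The omission does not show that the values will not be collected. It means that their timing must be confirmed.

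**Conclusion.** The concern holds in a limited form. Kidney function, as distinct from the NGAL injury marker, is compared only as a RIFLE incidence. Under assumed rates and 22 per group, Fisher's test has about 20% to 51% power for the five large contrasts and below 10% for the two moderate ones. That does not support the Conclusion's claim to determine the effect.

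A continuous analysis of the same measure could be much more powerful or about equally powerful, depending on whether the fluid shifts all patients or changes how many have a clear rise. A reader might infer that changing the scale would let the trial settle the renal question. It would not: for 30% against 20%, power remains below 20% at 22 per group even under the favourable model. The sample size is the main limit, so the renal result can only be exploratory. Every power figure rests on assumed rates; the article supplies only the group sizes, the test and the 5% level.

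**What to change.** 1. In Study endpoints and Statistics, keep RIFLE incidence with its risk ratio and 95% CI.
2. Beside it, prespecify a continuous comparison of the kidney-function measure used for RIFLE grading. One example is peak postoperative creatinine as a log ratio to the preoperative value, in a linear model adjusted for the log preoperative value, reported as a ratio of geometric means with 95% CI.
3. Reword the Conclusion so that the renal result is an exploratory estimate with its CI, and say that a non-significant RIFLE comparison will not be read as no renal difference.
4. Confirm when creatinine is measured, since it is absent from the sample lists under the time course of the study.

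The cost is wording and one extra secondary model. If the values needed for RIFLE are collected as that grading implies, no added patients or visits are needed. The downside is one more secondary analysis, on a scale that is less directly clinical than a RIFLE class.

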### Study intervention

An equal number of patients will be randomized to receive either Ringerfundin® solution or G5-K crystalloid solution as baseline infusion during the entire period that an intravenous administration of fluid is necessary (Table 1). The G5-K crystalloid solution is already used as a baseline infusion on our intensive care unit, and has been shown to be safe.

**Table 1 T1:** Electrolyte composition of the two different crystalloid solutions

**Electrolyte**	**Ringerfundin®**	**G5-K solution**
Sodium	145.0 mmol/l	50.0 mmol/l
Potassium	4.0 mmol/l	30.0 mmol/l
Magnesium	1.0 mmol/l	2.0 mmol/l
Calcium	2.5 mmol/l	0 mmol/l
Chloride	127.0 mmol/l	0 mmol/l
Acetate	24.0 mmol/l	0 mmol/l
Maleate	5.0 mmol/l	0 mmol/l
Lactate	0 mmol/l	18 mmol/l
HPO_4_	0 mmol/l	8.0 mmol/l
Glucose	0 mmol/l	50 g/l

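### The hypernatremia and hyperchloremia outcomes count only the direction that the comparator's composition promotes, and the electrolyte and osmolality outcomes use a window whose length is not fixed

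*Protocol article*

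**What the plan says.** In the protocol article, Study endpoints, the laboratory secondary outcomes are of three kinds.

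- **Incidences during the infusion:** "incidence of hypernatremia during the duration of infusion; incidence of hyperchloremia during the duration of infusion", and "incidence of hypokalemia or hyperkalemia during the duration of infusion". Sodium and chloride are counted upward only, potassium in both directions.
- **A change during the infusion:** "changes in plasma and urine osmolality during the duration of infusion", with no direction fixed.
- **Outcomes not tied to the infusion:** "difference in pH 24 hours postoperatively (metabolic acidosis defined as hyperchloremia, normal anion gap, low plasma bicarbonate", which is taken at a fixed time; and "changes in plasma renin, aldosterone, arginin-vasopressin, and BNP levels; and changes in NGAL urine values", with neither direction nor window.

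Study intervention says that the randomized solution is given "as baseline infusion during the entire period that an intravenous administration of fluid is necessary". No length is set.

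Objectives of the study (objective 2) compares pH, electrolytes, glucose and bicarbonate at 6, 24, 48, 72 and 96 hours in both arms, and the visit sections schedule those samples. Reporting of adverse events includes abnormal laboratory results in its definition. The Discussion part of the Abstract states: "This trial assesses the benefits and harms of two different balanced crystalloid solutions for perioperative fluid management".

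**The concern.** There are two separate problems.

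**Direction.** When two solutions differ sharply in sodium, chloride and glucose, each can be expected to push the blood values its own way. Counting events in one direction only gives an incidence table that can show the comparator's disturbances but not the opposite ones. The same list treats potassium symmetrically, so two-way counting was available. The one-way choice matches the hypothesis stated at the end of the Background (less hypernatremia and less hyperchloremic acidosis with G5-K). It sits less well with a stated aim of assessing harms as well as benefits.

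**Window.** The infusion period begins after randomization and ends when intravenous fluid is no longer needed. That end point may depend on recovery, and recovery is what the trial expects treatment to change. An incidence over such a period mixes the risk of the event with the time at risk. The article already has a fixed schedule for the same analytes under objective 2, so one variable is assessed over two different periods.

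A smaller point concerns the bracketed definition, "metabolic acidosis defined as hyperchloremia, normal anion gap, low plasma bicarbonate". Any count of acidosis based on it would miss acidosis without hyperchloremia or with a raised anion gap.

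**Working it through.** The article gives no figure of its own to reproduce here. The check sets the outcome list against the composition table and then illustrates the window effect.

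**1. Composition and daily baseline load.** Inputs: concentrations from Table 1, and 1,500 ml per 24 h from the section Postoperatively. Load = 1.5 l × concentration, Ringerfundin vs G5-K.

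- Sodium: 1.5 × 145 = 217.5 mmol vs 1.5 × 50 = 75 mmol. Counted: high only.
- Chloride: 1.5 × 127 = 190.5 mmol vs 1.5 × 0 = 0 mmol. Counted: high only.
- Potassium: 1.5 × 4 = 6 mmol vs 1.5 × 30 = 45 mmol. Counted: high and low.
- Glucose: 0 g vs 1.5 × 50 = 75 g. No incidence outcome.

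These are baseline loads only. Ringerfundin is also given as rescue and for blood loss in both groups, so the contrast actually received would be smaller.

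The listed chloride content of G5-K may be incomplete. Its cations sum to 50 + 30 + 2 × 2 = 84 mEq/l and its anions to 18 + 2 × 8 = 34 mEq/l (phosphate taken as divalent). The Background also speaks of reduced chloride, while the Discussion says the solution has none. If all of the missing 84 − 34 = 50 mEq/l were chloride, the contrast would be 127 vs 50, and the direction would be the same.

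**2. Which outcomes are one-way.** Only hypernatremia and hyperchloremia. Potassium can count against G5-K, whose potassium load is 45/6 = 7.5 times higher. Osmolality, pH difference, hormones, BNP and NGAL are undirected.

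**3. Window.** The article gives neither infusion lengths nor event rates, so both are assumed. With the same independent risk p per sample in both arms and k samples inside the window, the chance of at least one event is 1 − (1 − p)^k.

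- p = 0.10: five samples, 1 − 0.9^5 = 41.0%; four, 1 − 0.9^4 = 34.4%; three, 1 − 0.9^3 = 27.1%. Ratios to five samples: 0.344/0.410 = 0.84 and 0.271/0.410 = 0.66.
- p = 0.05: 22.6%, 18.5% and 14.3%. Ratios 0.82 and 0.63.
- p = 0.20: 67.2%, 59.0% and 48.8%. Ratios 0.88 and 0.73.

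At 22 patients per arm and p = 0.10, five vs four samples means 22 × 0.410 = 9.0 vs 22 × 0.344 = 7.6 patients with an event, although the treatments do not differ.

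**4. Acidosis.** The named outcome is a pH difference at 24 h. A fall in pH from any cause enters it, whatever the bracketed definition says. The definition would matter only if acidosis were tabulated as an event. The Intraoperatively section describes severe metabolic acidosis by base excess and pH with no chloride condition, so the article itself uses the term more widely.

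**The case against.** The strongest reply is that nothing is hidden. Objective 2 compares sodium, chloride, glucose, bicarbonate and pH at five fixed times in both arms, and abnormal laboratory results can be recorded as adverse events. A shift toward low sodium or high glucose under G5-K would therefore be seen. The one-way incidences follow the prespecified hypothesis, and testing a stated mechanism with secondary outcomes is legitimate. Oral fluids and diet start on the same schedule in both arms, and no rule links the end of infusion to defecation, so unequal duration is a possibility and not a stated fact. The illustration also assumes independent samples, whereas repeated values in one patient are correlated. A disorder that begins early and persists would be caught by either window.

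Most of this stands, and it rules out several stronger readings that a reader might infer:

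- That the laboratory outcomes as a whole favour G5-K by construction. Only two of them are one-way.
- That the window favours G5-K. It favours whichever arm stops sooner, and the article does not say which that would be.
- That non-hyperchloremic acidosis is excluded from the acid-base outcome. The pH comparison includes it.
- That the trial could not report harms. Objective 2 and the adverse event definition contradict this.

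The reply does not remove the asymmetry in the incidences. A comparison of mean concentrations does not show how many patients crossed a threshold, and adverse event recording is not the counterpart of a named outcome assessed in the same way in both arms. Nor is this detail left to an analysis plan, because the article itself fixes the directions and the window.

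**Conclusion.** The point holds in a limited form. Two secondary incidences, hypernatremia and hyperchloremia, count only the direction that the comparator's composition promotes, while hyponatremia, hypochloremia and hyperglycemia are not incidence outcomes. This follows directly from the outcome list and Table 1. Separately, the sodium, chloride, potassium and osmolality outcomes rest on a post-randomization window of unfixed length. Its possible effect is moderate: one sample fewer in one arm gives a spurious risk ratio of 0.82 to 0.88 for assumed per-sample risks of 5% to 20%. Those figures assume independent samples and unequal infusion lengths. The article supports neither the size nor the direction of any imbalance.

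The acidosis definition is a wording problem that would matter only if acidosis were counted as an event. The primary outcome is unaffected and no data are lost, so this is an inexpensive improvement to how secondary outcomes are reported, not a threat to the trial.

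**What to change.** - Count the sodium, chloride and potassium incidences, and assess osmolality change, over the scheduled 6, 24, 48, 72 and 96 h samples in all randomized patients, in line with the intention-to-treat analysis in Statistics. Keep the infusion-period version as a supplementary analysis, and report infusion length and the number of samples counted per arm.
- Report the incidences of hyponatremia, hypochloremia and hyperglycemia beside the existing ones, with thresholds set before the data are seen.
- Leave the 24 h pH difference as it is. If acidosis is also reported as an event, define it from pH with bicarbonate or base excess regardless of chloride, and show the hyperchloremic subtype separately.

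The cost is a change of endpoint wording and a few more rows in a secondary table; the samples are already scheduled. One drawback is that some samples will fall after the infusion has ended and may dilute differences present while it was running. The supplementary analysis is kept for that reason.
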